### Data collection

All women that register for prenatal care at a participating center will receive written information about the study. All women under 24 weeks of gestational age (GA) at inclusion who are able to communicate in Dutch (with assistance) will be asked to participate in the study. Their care provider will verbally inform the women at their first prenatal consultation (generally around 8–12 weeks of GA) and will ask them for informed consent. No exclusion criteria will be employed. Participation includes permission to collect women’s routine pregnancy outcomes as registered in the National Dutch Perinatal Data Registry (Perined, see end of this section) and optional agreement to fill out four self-administered questionnaires. For participants under the age of 18, informed consent of their parents or caregivers will be obtained.

#### Control group

Within the control period, all participants will be part of the control group and will receive usual individual prenatal care. See Fig. 1.

**Fig. 1 Fig1:**
[figure not shown]
Flow-chart data collection

#### Intervention group

Within the intervention period, pregnant women are offered perinatal care in the CP model. In the CP model traditional prenatal care with one-to-one visits with a perinatal care provider is replaced by the use of a group model [35]. Care is provided by a midwife or an obstetrician (facilitator) and a co-facilitator to groups of eight to twelve women of similar gestational age. Groups meet eight to ten times during pregnancy at the usual scheduled visits, with sessions running for 90 to 120 min. The usual prenatal health assessment is integrated with information, education and peer support. All involved care providers will be trained by licensed trainers to perform CP. The intervention period begins when the center starts to recruit for their first CP group, after the randomized time point. All women included in the study during this period will be part of the intervention group. In addition to the study information, participants will be informed about CP at their first prenatal consultation and will be given the choice to participate in CP. Women that do not participate in CP will receive usual individual care, resulting in two sub-groups within the intervention group. See Fig. 1.

We will use data from the Perined database. The Perined database contains linked and validated routine care information concerning pregnancy, delivery, (re)admissions and pregnancy outcomes [36]. Data are routinely and separately registered by midwives, obstetricians, general practitioners and paediatricians/neonatologists. For this study, the Perined data will be complemented with data from the questionnaires to be completed by participating women at four time points: Table 1 provides an overview of the timing of the different items. Reminders will be sent after 1, 2 and 3 weeks and participants will be reminded by their care provider. Finally, we will use implementation data from CP-group-evaluations and qualitative data from semi-structured interviews with care providers. Outcome measurements are described below. More details on instruments used in the questionnaires are provided in Table 2.

**Table 1 Tab1:** Overview of items in the questionnaires at four measurement time points

T1, inclusion (8–12 weeks of GA)	T2 (28 weeks of GA)	T3 (36 weeks of GA)	T4 (6 weeks postpartum)
Basic characteristics, current weight	Life style Knowledge (2)	Life style (3), medication use (2)	Life style (4), prenatal and perinatal health care use (2)
Life style and medication use	Life style (2)	Prenatal health care use	Labor experience, and emotions during labor
Preconceptional health care use	Depression	Prenatal Care Knowledge (2)	Breastfeeding initiation and duration
Life style- and Prenatal care Knowledge	Participation and experience of CP^a^	Stress and Coping (2)	Neonatal sleeping- and crying behavior
Stress and Coping		Social Support (2)	Self-efficacy in child care
Social Support		Readiness for Labor and Baby care	Depression (2)
Intended pregnancy education		Expectations on labor and child birth, intentions on infant feeding	Pregnancy education (2)
Intended participation CP^a^		Prenatal Care Satisfaction	Participation CP (3)^a^
		Participation and experience of CP(2)^a^	

^a^Complementary items for intervention group

**Table 2 Tab2:** Overview of instruments that will be used in the study

Tool	Constructs	Items	Scale — Analysis	Validation	References
Labor and birth outcomes					
Readiness for labor-item	On a scale of 0 to 100, where 0 is not at all and 100 is completely, how ready do you feel for labor and delivery?	1 item	0-100 – total score	Not available	Ickovics et al., 2007 [17]
Labor and Delivery Index (LADY-X)	Quality of received care and maternal emotions	7 items: e.g. “Information given by the healthcare professionals during childbirth.”	3 point scale^a^ – sum score (range 0–14)	Test-retest reliability, ICC^b^ > .80; Convergent and divergent validity *r* = .24-.61; Construct validity *p* < .001-.02.	Gärtner et al., 2015 [37]
Shortened Labor Agentry Scale (LAS-10)	Sense of control during childbirth	10 items: e.g.”I felt confident.”	7 point scale (almost always-rarely) – sum score (range 10–70)	A^c^ = .85-.97^d^	Hodnett and Simons-Tropea, 1987 [38] Geerts et al., 2014 [59]
Health literacy					
Prenatal/Postnatal care knowledge	Prenatal and postnatal care knowledge	19 items: e.g.” Babies of mothers who smoke tend to be smaller than babies of mothers who do not smoke.”	5 point scale (definitely false-definitely true) – sum score (range 0–95)	α = .65	Ickovics et al., 2007 [17]
Psychosocial outcomes					
Revised Prenatal Distress Questionnaire (NuPDQ)	Concerns about birth/baby, concerns about weight/body image, concerns about emotions/relations	9-17^e^ items: e.g. “Are you feeling bothered, worried or upset at this point in your pregnancy about taking care of a new born baby?”	3 point scale (not at all-very much) – sum score (range 0–34)	Test-retest reliability *r* = .75, α = .80-.81^d^	Yali and Lobel, 1999 [39] Yali and Lobel, 2002 [40] Alderlice et al., 2012 [41]
Cambridge Worry Scale (CWS)	Women’s major worries in pregnancy: socio-medical, health, socio-economic, and relational	17 items: e.g. “How much of a worry is your housing to you?”	6 point scale (not a worry-major worry) – at item level or using total (range 0–85) or factor scores	*Socio-medical* α = .71; *Health* α = .70; *Socio-economic* α = .29-.63; *Relational* α = .67. Test-retest reliability *r* = .69-.72	Green and Kafetsios, 1997 [42] Green et al., 2003 [47]
Coping (based on the Revised Prenatal Coping Inventory)	Problem focused active coping, emotion focused active coping, emotional passive coping	9 items: e.g. “How often did you try not to think about it?”	5 point scale (never-very often) – sum score per subscale (range 0–12)	Not available	De Ridder et al., 1996 [48] De Ridder et al., 1998 [49] Savelkoul et al., 2000 [50] Hamilton and Lobel., 2008 [51]
Social Support List-12 Interaction (SSL-12 I)	Daily support, problem support and appreciation support	12 items: e.g. “Do you get invited to a party or dinner sometimes?”	4 point scale (seldom-very often) – scale scores (range 4–16) and sum score (range 12–48)	*Daily support* α = .70-.80^d^; *Problem support* α = .72-.89^d^; *Appreciation support* α = .72-.82^d^.	Kempen et al., 1995 [60] Bridges et al., 2002 [53] Van Sonderen., 2012 [52]
Edinburgh Postnatal Depression Scale (EPDS)	Prenatal and postnatal depression The EPDS was originally developed for postnatal use, but was validated as a prenatal screening instrument.	10 items: e.g. “I have been able to laugh and see the funny side of things.”	4 point scale^a^ – sum score (range 0–30)	α = .80	Cox et al., 1987 [54] Murray et al., 1990 [61] Green et al., 1994 [62] Adouard et al., 2004 [63]
Parenting outcomes					
Readiness for baby care-item	“On a scale of 0 to 100, where 0 is not at all and 100 is completely, how ready do you feel for taking care of your baby?”	1 item	0-100 – total score	Not available	Ickovics et al., 2007 [17]
Parental Expectations Survey (PES)	Women’s self-efficacy in child care	25 items: e.g. “I can manage the feeding of my baby.”	10 point scale (cannot do-certain can do) – sum score (range 25–250)	α = .86-.91^d^	Reece et al., 1992 [55] Reece et al., 1998 [64] McCarter-Spaulding et al., 2001 [65]
Satisfaction with prenatal care					
Patient Participation and Satisfaction Questionnaire (PPSQ)	Participation in prenatal care and satisfaction	22 items: e.g. “Helpful information was given to me about my pregnancy.”	5 point scale (not applicable and very dissatisfied-very satisfied) – scale scores and total sum score (range 22–110)	*Participation* α = .93; *Satisfaction* α = .93; *Total* α = .95.	Littlefield et al., 1987 [56] Ickovics et al., 2007 [17]

^a^Verbal aspects vary per item

^b^Intraclass correlation coefficient

^c^Cronbach’s alpha

^d^Varying between studies

^e^Number of items vary depending on time point administered

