## Methods

### Design

This study will be performed in thirteen midwifery practices (primary care, low-risk population) and two hospitals (secondary care, moderate to high-risk population) that do not yet offer CenteringPregnancy within the region ‘northern South-Holland’ (an urban – sub-urban setting). A stepped wedge cluster randomized controlled trial design is chosen for several reasons. Firstly, randomization at individual level is not appropriate, as training professionals in CP will most probably also affect the non-CP consultations. Secondly, since midwifery care in the Netherlands is subjected to marketing forces, cluster randomization is expected to result in unfair competition between independent centers operating in the same region. Within the chosen design, all clusters (midwifery practice or hospital) start to collect control data at the same time (control period). Clusters will subsequently implement the intervention at a different, randomly selected time point and will then start to collect intervention data (intervention period). For this study, we will divide all fifteen centers into three groups and will randomly assign each group to one of three time points (steps) at which they will start to implement the intervention, with a between-step period of 3 months.

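### Condition follows the date of inclusion, so a woman first seen before her centre's switch can be included after it and counted as intervention; the date of first consultation is a firmer anchor

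*Protocol article*

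**What the plan says.** Under Intervention group, the protocol article first defines when the intervention period starts: "The intervention period begins when the center starts to recruit for their first CP group, after the randomized time point". It then gives the allocation rule: "All women included in the study during this period will be part of the intervention group". The Control group section is the mirror image: whoever participates during the control period is a control and has individual care. The date of inclusion, compared with the centre's switch, therefore decides the condition.

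Two sets of statements govern that date.

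- **Eligibility** (Data collection): "All women under 24 weeks of gestational age (GA) at inclusion who are able to communicate in Dutch (with assistance) will be asked to participate".
- **Planned timing** (Data collection), on when the woman's consent is sought: "Their care provider will verbally inform the women at their first prenatal consultation (generally around 8–12 weeks of GA) and will ask them for informed". Table 1 agrees, heading its first column "T1, inclusion (8–12 weeks of GA".

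Women hear of the study before that visit: "All women that register for prenatal care at a participating center will receive written information about the study". On the provider side, "All involved care providers will be trained by licensed trainers to perform CP". The Design section sets three steps, "with a between-step period of 3 months".

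The Data analysis section compares the control group with the complete intervention group and calls this intention-to-treat. The Discussion names one selection problem, the choice between CP and individual care within the intervention period.

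**The concern.** In a stepped wedge trial, randomisation protects the comparison only if the woman's place before or after the switch is settled by something that neither she nor her provider can adjust once the switch is in view. Here it is settled by inclusion, which depends on a provider asking and a woman agreeing. The care cannot be masked, the staff are trained for it, and the article describes no concealment of the time point.

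There is also a reason to wait. CP runs in groups of 8 to 12 women at about the same stage of pregnancy, and each centre has to assemble a first group. A woman already in care but not yet included could join that group and count as intervention. Had she been included at her first visit, she would have been a control with individual care.

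What is at stake is the main comparison. Its two groups are built from this date, so analysing everyone as included does not remove selection on the date. Multilevel terms for centres and CP groups deal with clustering, not with who was placed on which side. The article also means to read the difference between the intention-to-treat and per-protocol results as a sign of selection bias. That reading assumes the intention-to-treat groups are themselves free of it.

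**Working it through.** The article states no figure on this point, so there is none to reproduce. The check has three parts.

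**1. How far can inclusion trail the first visit?** Inputs: first consultation at 8–12 weeks and inclusion under 24 weeks (Data collection); steps 3 months apart (Design).

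- Longest delay = 24 − gestational age at first visit: 24 − 12 = 12 weeks to 24 − 8 = 16 weeks.
- One step = 3 × 52.18 / 12 = 13.0 weeks.

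The longest permitted delay is about one step. This is a ceiling for an individual woman, not an expected delay.

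**2. Does any rule close the gap?** The consent request is tied to the first consultation; the word generally qualifies only the gestational age at that visit. Late inclusion is therefore an exception to the described routine. But the binding limit is under 24 weeks, and the allocation rule refers to inclusion, not to first contact. The article does not require inclusion at the first visit, does not assign condition by registration or first visit, and does not exclude or reclassify women already in care at the switch.

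**3. What could it do to the result?** This is an illustration only, because the article gives neither the number of such women nor their risk. Take 800 women per condition and 14% morbidity (Sample size calculation), with no true effect of CP. Let d would-be controls with risk r be included after the switch instead.

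- Control rate = (800 × 0.14 − d × r) / (800 − d)
- Intervention rate = (800 × 0.14 + d × r) / (800 + d)

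| d (assumed) | r (assumed) | Control rate | Intervention rate | Apparent odds ratio |
|---|---|---|---|---|
| 80 (10%) | 10% | 104 / 720 = 14.4% | 120 / 880 = 13.6% | 0.94 |
| 160 (20%) | 7% | 100.8 / 640 = 15.8% | 123.2 / 960 = 12.8% | 0.79 |
| 80 (10%) | 14% | 14.0% | 14.0% | 1.00 |
| 80 (10%) | 18% (14 + 4 points, the mirror of row 1) | 97.6 / 720 = 13.6% | 126.4 / 880 = 14.4% | 1.07 |

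Size and sign both depend on the assumptions. There is no bias if the delayed women carry average risk, and it reverses if they carry higher risk.

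Now apply two ways of handling the women in row 1. Classified by first consultation, all 80 return to control: 112 / 800 = 14.0% on both sides, odds ratio 1.00. Excluded altogether, the rates are 104 / 720 = 14.4% and 112 / 800 = 14.0%, odds ratio 0.96. Exclusion alone therefore leaves part of the imbalance, because the control group stays depleted.

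**The case against.** The strongest reply is that the article plans inclusion at the first consultation. Consent is asked for there, Table 1 places inclusion at 8–12 weeks, and women in the intervention period are told about CP at that same visit. On this reading the 24-week limit is there for women who book late, and holding a woman back would depart from the plan. This stands to a large extent. Late inclusion is a permitted exception, not the expected course, and the article gives no evidence that anyone would delay on purpose. It does not close the gap, because the limit is not confined to late bookers and the allocation rule ignores the first visit.

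A second reply is that a journal article condenses a longer protocol, which may say how women already in care are handled, and that the flow chart is not visible here. That is fair as to procedures such as screening logs. The allocation rule, however, is stated in the article, and it is stated in terms of inclusion.

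A third is that the remedy has its own cost: straddling women who joined CP would be counted as controls. This stands and is taken up under the fix.

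A reader might also infer more than the document supports:

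- **That the bias favours CP.** The Background suggests CP may reach high-risk groups, so women drawn into a first group could as well be at higher risk.
- **That about half of control-period registrants could be moved.** This assumes four equal periods (6 of 12 group-periods are control, 3 of them just before a switch) and applies the longest delay to every woman.
- **That 120–180 women would be moved** (15 × 8 to 15 × 12). This requires every first group at all 15 centres to consist of held-back women, although recruitment for that group starts with the intervention period and new registrants can fill it.

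**Conclusion.** The point holds as a weakness in the allocation rule. Condition rests on a date that can fall on either side of a known switch for a woman already in care, with at most 12–16 weeks of room. The planned analyses do not correct for selection through that route.

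The stronger reading, that providers or women will in practice choose the condition and that the result will be tilted towards CP, is not supported. The number of women and the direction of any bias are unknown. The odds ratios of 0.79 to 1.07 in the illustration follow from assumed shares and risks and are not estimates. The change is worth making because it is cheap and because it writes the article's own intended point of contact into the rule.

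**What to change.** In the Intervention group section, with a matching line under Control group, state that for the intention-to-treat analysis a woman belongs to the condition her centre was in on the date of her first prenatal consultation there, whatever the date of consent or inclusion. Add a sensitivity analysis that excludes women first seen before the switch but included after it, and report how many there were in each centre.

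The cost is one sentence and one date per woman from the centre's record. The first-consultation date is not wholly beyond influence, but it is harder to shift than the date of consent.

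The downside should be stated openly. Straddling women who joined CP will sit in the control group and dilute the contrast. The sample size section aims at an upper confidence limit below 1.85, and there dilution pulls towards no difference and so makes the aim easier to meet. The sensitivity analysis removes this dilution. As the working shows, it can leave part of the selection in place, so it should be read beside the main analysis and not in its stead. If straddling women prove numerous, a stricter variant that excludes everyone first seen in the 12–16 weeks before a centre's switch, whenever included, would avoid both problems at the price of a smaller control group.

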#### Health behavior outcomes and health literacy

Health behavior outcomes and health literacy will be collected using the questionnaires. Health behavior outcomes are: physical activity (number of 30-min exercise per week and self-judgment physical activity), nutritious behavior (breakfast-, vegetable-, fruit-, juice- and snack-consumption, and self-judgment eating behavior), substance use (tobacco-, alcohol-, and soft or hard drug consumption, and intentions towards smoking cessation), medication use (folic acid use and use of (prescribed) drugs), intention of infant feeding and attitude towards breastfeeding, and infant feeding on day one, at 1 week postpartum and at 6 weeks postpartum. Women’s prenatal and postnatal care knowledge will be measured with a scale developed by Ickovics et al. [17].

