### Statistical issues

#### Sample size calculation

A minimal sample of 600 pregnant women in both the intervention and control condition is needed to be able to accept with 95% confidence and an upper confidence limit less than 1.85, that after the intervention has been implemented, there is at least no significant difference in infant morbidity (using 14% of infant morbidity as outcome) between CP and individual care. This sample size is also largely sufficient to find amongst others a difference in prenatal care satisfaction or in proportion of breastfeeding comparable to Ickovics et al, with an α of 0.05 and a power of 0.90 [17]. We will account for a 20% loss to follow-up and aim to include in total 1600 women (800 in both conditions).

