## Discussion

Former research has shown a positive effect of CP, including a higher birth weight and more prenatal care satisfaction, however the findings were inconsistent [17, 26, 27, 30, 31]. Furthermore, due to differences in population characteristics and health care system, previous findings cannot be directly extrapolated to the Dutch setting. Our study aims to contribute to the evidence regarding the effect of CP and will give a first indication of the effect and implementation of CP in a Western high-income society other than the USA. Also, by measuring factors that are hypothesized to mediate the effect of CP, we aim to be able to explain the mechanisms that lead to eventual found effects on maternal and neonatal outcomes.

A strength of our study lies in the stepped wedge cluster design. In this design, participating practices are randomly assigned to the period in which they will start providing CP and will function as their own control group before implementing CP. Also, it allows to take into account time effects. Another strength of the study is the use of routine data to assess several neonatal and maternal outcome measures.

One limitation however is the fact that centers are not yet trained in CP and that it takes some time to implement, which may lead to less model fidelity and smaller effect sizes. Fidelity to facilitate group processes in CP and content fidelity are known to associate with significant reductions in preterm birth and intensive utilization of care [58]. To gain more insight in the effects of fidelity of the model as provided by health care providers we will collect data on process and implementation, and will relate it to the effects of CP. The possibility of selection bias by letting women choose between CP or individual care is another limitation of our study. To be able to estimate the degree of selection bias, we will collect numerous demographic and psychosocial data of both groups in the intervention period (CP-participants and Non-CP-participants), also allowing us to correct for differences in basic characteristics. In addition, we will perform an intention-to-treat analysis, as well as a per protocol analysis. Differences in results of both analyses will provide an indication of assumed selection bias.

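### Infant-feeding intention is first measured at 36 weeks, so the per-protocol breastfeeding comparisons can be corrected only in part for women's own choice of CP

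*Protocol article*

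**What the plan says.** Table 1 sets out four questionnaires: T1 at inclusion (8–12 weeks), T2 at 28 weeks, T3 at 36 weeks and T4 at 6 weeks postpartum. Feeding intention appears once, in the T3 column: "Expectations on labor and child birth, intentions on infant feeding". The feeding outcome comes at T4: "Breastfeeding initiation and duration". The T1 and T2 columns name no infant-feeding item.

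The section on health behavior outcomes and health literacy classes intention as an outcome alongside feeding itself: "intention of infant feeding and attitude towards breastfeeding, and infant feeding on day one, at 1 week postpartum and at 6 weeks postpartum".

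On exposure, the Intervention group section states: "Groups meet eight to ten times during pregnancy at the usual scheduled visits". In the intervention period each woman "will be given the choice to participate in CP", and those who decline receive individual care.

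Under Data analysis, the intention-to-treat comparison sets the control group against the complete intervention group. The per-protocol analysis compares control women, CP-participants and non-CP-participants. The Discussion names selection bias from this choice as a limitation. Its answer is to collect demographic and psychosocial data, "also allowing us to correct for differences in basic characteristics". The Sample size calculation says that 600 women per condition suffice, at 0.90 power, to detect "a difference in prenatal care satisfaction or in proportion of breastfeeding" as large as in an earlier trial. It gives these as examples in an open-ended list.

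**The concern.** Breastfeeding is a postpartum event and has no baseline of its own. The closest substitute is the woman's intention early in pregnancy, before CP can have influenced it. The schedule takes intention only at T3, when it may already reflect what was taught in the group. Adjusting for the T3 value when estimating the effect of CP could therefore remove part of that effect, and leaving it out leaves prior intention uncontrolled.

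This matters where women sort themselves into groups. If women who already plan to breastfeed are readier to join a group education model, CP-participants will breastfeed more even if CP does nothing. The gap cannot be filled later: once a woman has begun CP, her prior intention can no longer be recorded, whatever the analysis plan says. The intention outcome at T3 likewise has no earlier value to compare with.

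**Working it through.** **1. Is there really no earlier measurement?** Table 1 numbers its repeats: stress and coping, and social support, carry a (2) at T3, and life style runs from (2) to (4). Feeding intention at T3 carries no number and has no entry at T1 or T2. T1 does list other intentions as separate items (pregnancy education and, in the intervention group, CP participation). The stated schedule therefore takes feeding intention once, at 36 weeks.

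**2. Is T3 after exposure?** There are eight to ten sessions during pregnancy. The week of the first session is not stated, but most sessions would normally fall before 36 weeks.

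**3. What remains for adjustment?** Age, country of birth, religion, education, marital status, employment and parity (Basic characteristics). Table 1 adds, at T1, life style and medication use, knowledge, stress and coping, social support and intended pregnancy education. These are usable predictors. The specific one is missing.

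**4. Size of the unadjusted bias, CP versus non-CP.** The protocol gives no breastfeeding or intention rates, so all inputs here are assumptions: breastfeeding in 70% of women with prior intention and 20% of those without, and no effect of CP.

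Spurious difference = gap in prior intention × (0.70 − 0.20)

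| Gap in intention | Spurious difference |
|---|---|
| 5 points | 0.05 × 0.50 = 2.5 points |
| 10 points | 0.10 × 0.50 = 5.0 points |
| 15 points | 0.15 × 0.50 = 7.5 points |

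The result depends on the assumed rates. With a 10-point gap, 70% versus 30% gives 0.10 × 0.40 = 4.0 points, and 90% versus 5% gives 0.10 × 0.85 = 8.5 points.

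**5. CP versus control.** If control women have the same average intention as the whole intervention group, the relevant gap is (1 − uptake) × the CP versus non-CP gap. For a 10-point gap and the 70%/20% rates, uptake of 30%, 50% and 70% gives 0.07, 0.05 and 0.03 × 0.50, that is 3.5, 2.5 and 1.5 points. The bias is smaller here, in the same direction.

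**6. Effect on a test.** Assume 300 versus 300 women and a breastfeeding rate near 55%. SE = √(0.55 × 0.45 × 2/300) = 0.041. A 5-point shift is 0.05/0.041 = 1.23 SE, and P(|Z + 1.23| > 1.96) ≈ 0.23 instead of 0.05. This ignores clustering and assumes that the T1 variables capture none of the gap. It is an unadjusted, upper-end illustration for a 10-point gap.

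**7. Intention-to-treat.** Take an overall rate of 70% in the intervention group and a 10-point CP versus non-CP difference due to selection alone. At 30% uptake the mix is 0.3 × 77% + 0.7 × 67% = 70%. At 50% it is 0.5 × 75% + 0.5 × 65% = 70%, and at 70% it is 0.7 × 73% + 0.3 × 63% = 70%. Choice of CP cancels out.

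**8. Possible gain in precision.** If T1 intention explained 10%, 20% or 30% of the variance (assumed), the SE in a linear or risk-difference model would be multiplied by √(1 − R²) = 0.95, 0.89 or 0.84. This does not carry over to a logistic odds ratio.

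**9. The 0.90 power.** It cannot be reproduced, because the article gives no breastfeeding rates. With 600 per condition, two-sided 0.05 and no clustering, the difference detectable at 0.90 power is 9.3 points at an assumed control rate of 40% or 50%, 8.9 at 60%, 8.2 at 70% and 6.9 at 80%. The statement is plausible for differences of that order, and the present point does not depend on it.

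**The case against.** The strongest reply is that the protocol already discloses selection bias, collects many T1 variables to correct for it, runs an intention-to-treat analysis beside the per-protocol one, and reads their difference as a sign of selection. Much of this stands, and it rules out several stronger readings that a reader might infer.

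- *That breastfeeding has no pre-CP predictor and selection cannot be corrected.* Not supported. Education, parity, country of birth, knowledge, social support and intended pregnancy education are all taken at T1, and the last bears directly on the supposed motive for choosing CP. Correction is partial, not impossible.
- *That the power statement for breastfeeding is undermined.* Not supported. It concerns the two conditions, 600 women each, which is the intention-to-treat contrast, and choice of CP does not bias that contrast. The article claims no power for the subgroups. Breastfeeding is a secondary outcome, named there as an example.
- *That breastfeeding-attitude items also sit at T3.* Not stated. Attitude is listed as an outcome without a time, and Table 1 has no line for it.
- *That intention-to-treat loses precision.* Nothing is lost; an optional gain is forgone.

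It is also fair that Table 1 is an overview and the questionnaires are not shown. If the T1 questionnaire does contain a feeding-intention item, the point falls away. The table's separate listing of other intentions at T1 makes that unlikely.

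What the reply does not answer is that disclosing selection bias does not supply the missing measurement. For this outcome the most direct selection variable is not scheduled before exposure.

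**Conclusion.** The point holds as a limited, inexpensive improvement to a planned secondary analysis. The protocol contains no contradiction or miscalculation here. The per-protocol breastfeeding comparisons may keep residual confounding by prior feeding intention after adjustment for the T1 variables. On the assumed 70% and 20% rates and a 5 to 15 point gap between CP and non-CP women, the unadjusted bias is 2.5 to 7.5 points. It is smaller against the control group, and smaller again to the extent that the T1 variables stand in for intention. The size of the real gap, CP uptake and breastfeeding rates are all unknown from the document. The conclusion also assumes that T1 is completed before a woman's first CP session and that most sessions precede 36 weeks.

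**What to change.** Add the infant-feeding intention item used at T3 to the T1 questionnaire for all participants. In the three-subgroup comparison, adjust the feeding outcomes (day one, 1 week and 6 weeks) and T3 intention for the T1 value, together with the T1 variables already planned. The same covariate may be used in the intention-to-treat analysis for precision, but this is optional. State that T3 intention is an outcome and will not be a covariate when the effect of CP is estimated. State also when breastfeeding attitude is asked, since the article does not say.

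The cost is a slightly longer questionnaire at inclusion and one more covariate. Women who have already passed T1 cannot supply the value afterwards, so the change helps only those enrolled after it is made.
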